#### Web- based goal tracking and education

In the time between monthly visits to the public schools for lesson plans and small group meetings, (S)partners will communicate with the school children via a secure website  which is monitored by study coordinators graduate students and faculty. This web-based platform allows for the facilitation of behavioral goal setting for nutrition and physical activity using a behavioral tracking tool, as well as links to educational modules to promote the achievement of heart healthy behavioral and educational goals and reinforce classroom educational efforts. Our protocol is developed based on previous relevant research involving goal setting [35,36,47-50] and knowledge gained from the pilot study. Students are required to log on weekly at school and set their activity and nutrition goals for the week, which will be measurable and based on national guidelines for nutrition and physical activity [51-54]. Students will maintain the same goal for a minimum of three weeks or until they achieve it. For example, a student who reports a low intake of whole grains (1 serving per day) may set a goal to have 3 or more servings of whole grains per day. Success will be based on achieving the goal at least 5 of 7 days per week. The students will log their progress for their nutrition and physical activity goals on tracking cards and then they will log their progress weekly on the (S)partner website. The (S)partners will give guidance to help them achieve the goal. To avoid barriers to computer access, there will be a set time weekly at the school during which the 5^th ^grade students report on their goals and communicate with their (S)partner. If children have access at home, they will be encouraged to access the website more often.

#### School Support

To promote healthful lifestyle behaviors among the school staff and promote support for the (S)Partners for Heart Health program, school staff will receive monthly newsletters and will be invited to attend an evening meeting which summarizes the (S)partner activities and provides tips for promoting nutrition and physical activity at school two times per year (once in the fall and once in the Spring). Additionally, school staff will be given access to the (S)partner website that will include links and materials they can access. The school principal will read nutrition and exercise promotion tips over the school intercom weekly and an informational (S)partners for Heart-Health bulletin board will be posted monthly in a central location in the school throughout the year.

#### Parental support and involvement

To promote parental understanding and support of (S)partners for Heart Health, parents of the 5^th ^grade students will receive monthly newsletters including encouragement to access the (S)partners for Heart Health website that will include links and materials they can access. They will receive a copy of their child's CVD risk factor profile immediately following baseline measurement with specific tips to help their children sustain or achieve healthful, physical activity and nutrition patterns. They will also be invited to attend the evening meetings (one in the fall and one in the spring) to summarize the (S)partner activities and provide tips for promoting nutrition and physical activity outside of school.

#### Measurement protocol

Assessments will be conducted during September (pre-intervention) and May (post-intervention) by MSU medical students and staff. This service is part of the medical students' community outreach elective and is an ongoing elective that will promote cost-effective, long-term sustainability of the study protocol. The assessment includes physical activity and nutrition behaviors; lifestyle and heart health knowledge, attitudes and behaviors for nutrition and physical activity; and self-efficacy toward nutrition and exercise behavioral goals. The CVD risk appraisal includes resting blood pressure, blood cholesterol, C-reactive protein, body size and composition, and aerobic fitness. The baseline assessment data will help guide the heart healthy nutrition and exercise goal setting mentioned in the previous section.

#### Knowledge, attitude, behavior and self-efficacy evaluations

A battery of surveys that includes questions about heart health knowledge, attitudes and self-efficacy toward lifestyle will be completed by the child. The nutrition, exercise, and heart health knowledge and attitude tools include materials and methods used in previous heart health research in children and the surveys included in the JIFF manual [42,55,56]. Self efficacy for nutrition, exercise and heart health behaviors will be assessed using a 5-point scale appropriate for children that uses circles from small to large reflecting level of confidence [57,58].

#### Habitual free-living physical activity

Habitual, free-living physical activity will be assessed by a pedometer (Digiwalker 200-SW) over a 1-week period. The subjects will be given instructions for wearing the pedometer during the school day. Prior to wearing their assigned pedometers, students will check them using the shaker test and the 10-step test. Pedometers that do not function properly during these 'validity' checks will be replaced. Participants will record the time on/time off and number of steps accumulated on a customized index card. Subjects will also record comments related to activities performed while not wearing the pedometer and other comments regarding any compliance-related issues. To be included in the statistical analysis, participants must wear the pedometer at least 4 days (3 week day and 1 weekend) for at least 10 hours. Data will be expressed as both the number of steps per day and percentage of days for which national recommendations for the number of steps per day (13,000 and 11,000 steps per day for boys and girls, respectively) are achieved [59-61]. The weekly amount of time viewing television, playing video games, and online computer use will be self-reported by the child. Children will also be asked to indicate the number of hours they watch/play on weekdays and weekends for each of the three screen media. The percentage of students viewing ≤ 2 hours per day of screen time [62] will be determined.

#### Dietary intake

Dietary intake will be assessed using the Block Kids Food Frequency Questionnaire for Kids (Block Dietary Data Systems, Berkeley, CA; ). Program staff will be trained to administer the survey per company instructions in a standardized manner. The administration will take place in a class room group setting. Following completion of the questionnaires they will reviewed by staff for completeness and mailed back to Nutriquest for analysis. The report includes daily estimates of macro-nutrients, major micro-nutrients, and servings per day of key food groups. It is established that fifth grade ages are a difficult age group to measure dietary intake in. A couple of recent studies have evaluated the validity of the Block Kids Food Frequency Questionnaire using age groups similar to our study population's ages. When comparing a single 24-hour recalls to the Block Questionnaire modest interclass correlations (≥ 0.30) were revealed for key nutrients, except for protein and fruit and vegetable servings [63]. However in another study that used three day food logs (versus a single 24-hour recall) for estimates of 100% juice, milk, calcium, and vitamin D intakes the correlations were higher (r = 0.51–0.55) [64].

#### Cardiovascular disease risk factors

As previously indicated, the CVD risk factor profile will include: body mass index (BMI), body fat, waist circumference, resting blood pressure, blood cholesterol, C-reactive protein, and aerobic fitness. Obesity indicators will include measurements of body size and composition. The BMI will be calculated from measured stature and body mass according to standardized procedures. Waist circumference will be measured using a Gullick Anthropometric Tape at the level of the umbilicus. For anthropometric indices, the medical students will be trained prior to data collection by the investigators, and intra- and inter-observer measurement error will be determined. This type of training protocol has resulted in small measurement errors during the actual measurement period (SEM = 0.3 cm standing height; 0.1 kg body mass; 0.2 cm WC). Body fatness will be estimated using a foot-to-foot bioelectric impedance device (Tanita Corporation, Tokyo, Japan). Resting blood pressure will assessed using manual blood pressure device with the appropriate sized cuff on the subject's upper right arm following standardized procedures recommended by the Joint National Committee (USA) on Prevention, Diagnosis and Management of Hypertension [65]. Blood samples will be obtained by fingerprick and collected in heparinized capillary tubes. Blood sampling by fingerprick has been chosen for reasons of compliance and feasibility. Compared to venipuncture, blood sampling by fingerprick is less invasive and is less likely to deter subjects from participating; fingerprick is also more feasible for a field-based setting. One sample will be analyzed for total cholesterol, high-density lipoprotein-cholesterol, and triglycerides within 5 minutes by a portable cholesterol/glucose analyzer according to the protocol of the manufacturer (Cholestech LDX System, Hayward, CA). A second sample will be analyzed for C-reactive protein also using the Cholestech LDX. Cardiorespiratory fitness will be estimated using the PACER test which consists of an endurance-type shuttle run which will be conducted by program staff trained to conduct this procedure following standardized procedures [66].

#### Process evaluation (protocol compliance)

Protocol compliance will be conducted throughout the study to determine how dose delivered and fidelity to each component of the intervention relate to 5^th ^grade student outcomes. Physical education teachers will use checklists to keep track of when they are conducting lessons, and the project coordinator will randomly observe selected lessons at each intervention school. In addition, teachers will be asked to record any modifications and/or feedback they have regarding lessons and will report this information to project staff during interviews (post-intervention). Checklists and observations will be used to assess changes related to school environment (bulletin board, principal announcement, newsletters, and meetings). Physical education teachers and principals will also be queried about school environment during interviews (post-intervention); this includes documenting secular changes at control schools via interviews. MSU student (S)Partners will submit goal sheets created with the 5^th ^grade students. Attendance will be taken at each activity requiring (S)Partner presence, and each (S)Partner will complete a survey regarding his/her experiences (midpoint and post-intervention). Project staff will monitor log-ins to the website and content of (S)Partner/5^th ^grade student interactions. Finally, 5^th ^grade students will report their perceptions of the JIFF lessons, the web-based reporting tool, and experiences with (S)partners.

#### Statistical Power Calculations

A power calculation indicated that based on an N of 180 and 90 children in each group (SPartners for Heart Health versus comparison group), the following changes will need to be achieved for the primary aims of this study. With respect to the percentage of students achieving the national recommendation for physical activity; based on an estimate of 50% of the students achieving physical activity guidelines at baseline, it will be possible to detect a difference of 18% in the percentage achieving the guidelines (an increase from 50% to 59%) with an alpha level of 0.05 and a power of 80% using a one-tailed test. For nutrition behavior we chose total dietary fiber intake since it is surrogate marker of fruit, vegetable, whole grain and legume intake. Based on an estimated baseline mean intake of 12 ± 8.8 grams of dietary fiber per day, it will be possible to detect a difference of 3.3 grams of fiber per day with an alpha level of 0.05 and 80% power using a one-tailed test.

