## Methods/Design

### Effectiveness study population and recruitment

This parallel design intervention trial has been approved by the MSU Institutional Review Board. Also approval from each of the participating school's board of education was also obtained.

Inclusion criteria for the effectiveness study includes 5^th ^grade classrooms within 50 miles of MSU with 25% or more of students qualifying for free or reduced lunch to ensure a portion of the population are at an increased risk of health disparities. Four schools will participate in the effectiveness trial. Two physical education classrooms (one boys and one girls) within each school will be included for a total of eight physical education classes. Two of the participating schools will be assigned to the (S)partners for Heart Health protocol and the other two will be assigned as the usual care comparison school. Depending on the school, physical education class size will vary from 25–35 students. We anticipate the total number of students will be approximately 180–200.

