Despite the many strengths of the intervention, there are some potential limitations. To date, we have only conducted a small pilot and feasibility study to prepare for the upcoming effectiveness study. Although formative assessment and the pilot have been performed, the goal of the upcoming investigation is to gain further information that will assist with a larger-scale implementation of the intervention. Thus, given the small number of schools that will be involved in the effectiveness study, it will not be possible to perform school-level analyses. In addition, schools were not randomized and blinding is impossible. Furthermore, over a 9-month period it will be a challenge to observe significant between group changes when comparing the (S)partner intervention with control schools. Other potential limitations that are difficult to anticipate but will be documented are concurrent health initiatives that may begin in a community during the effectiveness study. Finally, the number of (S)partners and medical students available and willing to be involved with this project during any given semester could be limiting to the number of schools and public school students that are served.

In summary, we have described the background and rationale, study design, measurement procedures, intervention components, and process evaluation procedures for (S)Partners for Heart Health. We anticipate this intervention will lead to an effective heart healthy education and behavior change model that can be cost effectively adopted into public schools to promote a desirable CVD risk factor status in school children. This will be achieved in part by using existing resources (MSU Extension) and activating college students (medical students and allied health professional students) in service learning through independent- and elective- academic credit, that offer training and experiential learning that cannot be achieved in the classroom setting. Although we are currently implementing this program in 5^th ^grade classrooms, the same methods can be applied to other grades with minor modifications (e.g., selection of different curricula). Ultimately, this program aims to reduce premature morbidity (obesity, hyperlipidemia, hypertension, diabetes, etc.) and mortality and their associated health costs by sustaining or improving heart healthy behaviors that influence CVD risk factor status in 5^th ^grades students acutely and long-term.

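### The stated 80% power and 5% one-sided error hold only for a child-level test on independent children, but whole schools are assigned, two per arm

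*Protocol article*

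**What the plan says.** The population and recruitment section fixes the design. "Four schools will participate in the effectiveness trial", and "Two of the participating schools will be assigned to the (S)partners for Heart Health protocol", with the other two as usual-care comparison. Each school contributes one boys' and one girls' physical education class, eight classes in all. The expected total is about 180 to 200 children.

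The Statistical Power Calculations section begins: "A power calculation indicated that based on an N of 180 and 90 children in each group". It gives a detectable difference of 18% in the proportion meeting activity guidelines, from a 50% baseline, and of 3.3 g/day of fibre (mean 12, SD 8.8), both "with an alpha level of 0.05 and a power of 80% using a one-tailed test". It mentions no ICC, design effect or between-school variance.

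The Discussion says that "given the small number of schools that will be involved in the effectiveness study, it will not be possible to perform school-level analyses". It adds that schools were not randomised, and it defers school-level methods, with linear mixed models as the example, to a later and larger trial.

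**The concern.** Children in one school share a PE teacher who may modify the lessons, and in the intervention schools also the principal's announcements and the bulletin board. The Discussion itself expects concurrent health initiatives in a community. Outcomes within a school are therefore likely to be correlated, and the arm comparison carries the variation between four schools as well as the variation between 180 children.

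A calculation that ignores this overstates power. A child-level test that ignores it finds significant differences more often than its nominal rate when there is no effect. At stake is how much weight the results on activity and nutrition behaviour, the first primary aim, can bear.

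**Working it through.** **Inputs.** From the article: 90 children per arm, 4 schools, 2 per arm, one-sided alpha 0.05, baseline 50%, difference 18% read as 18 points (50% v 68%), fibre SD 8.8 and difference 3.3. Children per school: 180/4 = 45. The ICC is not in the article; I assume 0.01, 0.02 and 0.05.

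**Step 1: reproduce the stated figures with independent children.**
- Fibre: SE = 8.8 × √(2/90) = 1.312. Power = Φ(3.3/1.312 − 1.645) = Φ(0.871) = 80.8%.
- Activity (pooled variance under the null, unpooled under the alternative): null SE = √(2 × 0.59 × 0.41/90) = 0.0733; alternative SE = √((0.25 + 0.2176)/90) = 0.0721. Power = Φ((0.18 − 1.645 × 0.0733)/0.0721) = Φ(0.824) = 79.5%.

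Both are close to 80%, so the stated figures correspond to a design effect of 1.

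**Step 2: allow for clustering by school.**
- Design effect DE = 1 + (45 − 1) × ICC; effective n per arm = 90/DE.
- True one-sided error of an unadjusted child-level test = 1 − Φ(1.645/√DE). At ICC 0.02: 1 − Φ(1.645/1.371) = 11.5%.
- Power: the Step 1 formulas with 90/DE in place of 90. This keeps a normal reference distribution, which is generous with four schools.

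**Step 3: school-level t test.** Degrees of freedom = 4 − 2 = 2. Power comes from the noncentral t. The noncentrality needed for 80% power is 3.98, against 2.49 for the normal. Detectable fibre difference = 3.98 × 1.312 × √DE; at ICC 0 this is 5.2 g.

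| ICC | DE | True error, unadjusted child-level test | Activity power, with DE | Fibre power, with DE | Activity power, 2 df | Fibre power, 2 df | Detectable fibre, 2 df |
|---|---|---|---|---|---|---|---|
| 0 | 1.00 | 5.0% | 79.5% | 80.8% | 50.2% | 50.7% | 5.2 g |
| 0.01 | 1.44 | 8.5% | 65.8% | 67.4% | 40.3% | 40.7% | 6.3 g |
| 0.02 | 1.88 | 11.5% | 55.9% | 57.5% | 34.2% | 34.5% | 7.2 g |
| 0.05 | 3.20 | 17.9% | 39.1% | 40.6% | 24.9% | 25.1% | 9.3 g |

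The ICC 0 row separates two effects. The fall from about 80% to about 50% comes from having only 2 degrees of freedom; the further fall comes from the correlation.

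**Sensitivity.** If clustering were by class only (22.5 children per class, DE = 1 + 21.5 × ICC), the error would be 6.8% and fibre power 74% at ICC 0.01, and 12.7% and 54% at ICC 0.05.

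**The case against.** The strongest defence is that the article is open about its limits. The abstract calls this a pilot effectiveness study. The Discussion names the small number of schools, the lack of randomisation and the difficulty of seeing significant differences between groups, and it gives informing a larger implementation as the goal. That stands as disclosure, but none of it alters or qualifies the power statement. A comparison of four school means is also possible, only imprecise.

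A second defence is that the size of the problem rests on assumed ICCs, and that the September and May assessments allow baseline adjustment, which could reduce the variation between schools. This also stands. The figures are a range, and they do not model baseline adjustment.

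Four stronger readings are tempting, and the article does not support them:
- **That unadjusted child-level tests are planned.** Powering on children and excluding school-level analysis points that way, but no analysis model is stated.
- **That a false positive would trigger the larger trial.** The Discussion plans that trial unconditionally. Its condition about effectiveness concerns whether the model could be sustained long term.
- **That a child-level test will declare effectiveness because of school differences.** At error rates of 8.5% to 18%, it may do so too often; that is all the figures show.
- **That a school-level one-sided p-value cannot fall below 1/6**, because four schools split 2:2 in only six ways. That floor takes its justification from random assignment, which the Discussion says did not occur.

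**Conclusion.** The point holds for the power statement. The 80% power and 5% error are given without qualification, and they are properties of a child-level test with zero within-school correlation. With any positive school ICC, an unadjusted child-level test has neither. Under a school-level test on 2 degrees of freedom, the 18 points and 3.3 g have only about 50% power even at ICC 0, so describing the figures as valid whenever the ICC is zero would still be incomplete.

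Over the assumed ICC range of 0.01 to 0.05 with 45 children per school, error is about 8.5% to 18%. Power for 18 points is about 66% down to 39% after a design effect, and about 40% down to 25% on 2 degrees of freedom. The direction does not depend on which ICC is chosen; the size does. The activity figures read the stated 18% as percentage points, which is the reading that reproduces 80% power. The article's parenthesis (50% to 59%) is a separate discrepancy.

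**What to change.** 1. **Statistical Power Calculations:** state that the 18 points and 3.3 g assume a child-level test with independent children. Add clustered figures over a stated ICC range, including the 2-degree-of-freedom result at ICC 0.
2. **Analysis:** do not rest an effectiveness claim on unadjusted child-level p-values. Report the baseline-adjusted arm difference from school means, with a confidence interval on school-level degrees of freedom. Adjusting at child level before averaging, or using change scores, keeps both degrees of freedom. Note that this does not remove bias from non-random assignment of schools.
3. **Reporting:** give the observed ICCs, with their uncertainty, for planning the larger trial.
4. **Discussion:** say that this study gives estimates and feasibility information and cannot by itself establish effectiveness. Replace the remark that school-level analysis is impossible with one that it is imprecise.

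The cost is wording and a small amount of analysis. Stated power will be lower and intervals wider. No extra schools are needed for this correction; enrolling more children in the same four schools would not add school-level degrees of freedom.

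### The physical-activity power statement does not hold as written: 50% versus 59% with 90 children per group has about 33% power, not 80%; the 80% belongs to 50% versus 68%

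*Protocol article*

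**What the plan says.** The section Statistical Power Calculations fixes every input for physical activity, which is part of the first primary aim.

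- Size and comparison: "based on an N of 180 and 90 children in each group (SPartners for Heart Health versus comparison group").
- Starting rate: "based on an estimate of 50% of the students achieving physical activity guidelines at baseline".
- Detectable effect, written in two ways: "it will be possible to detect a difference of 18% in the percentage achieving the guidelines (an increase from 50% to 59"%).
- Error rates: "with an alpha level of 0.05 and a power of 80% using a one-tailed test".

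It does not say whether the 18% is absolute or relative. A parallel calculation for dietary fibre follows, with the same alpha, power and sidedness. Its starting point is an assumed mean of 12 g per day with a standard deviation of 8.8 g, and its conclusion is that "it will be possible to detect a difference of 3.3 grams of fiber per day".

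**The concern.** The two expressions of the effect differ by a factor of two if 18% is a difference between percentages, which is how the sentence words it: 59 − 50 = 9 points, not 18. They agree only if 18% is relative (0.09 / 0.50 = 0.18). The question is which version, if either, goes with 90 per group and 80% power.

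This is the only power statement for physical activity. If the 59% is wrong, readers will think that the trial is sensitive to a 9-point gain when it is not, and a non-significant result could be taken as evidence against a modest benefit. The Discussion plans a larger trial to follow this one, so the misreading could carry forward.

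**Working it through.** **Inputs**, all from Statistical Power Calculations: n = 90 per group, two groups, one-sided alpha 0.05 (z = 1.645), power 80% (z = 0.842), reference rate 0.50; for fibre, SD 8.8 g and difference 3.3 g.

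**Step 1. Identify the section's method from the fibre figure.** The detectable difference for two independent means is (1.645 + 0.842) × SD × √(2/n).

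- √(2/90) × 8.8 = 1.312
- 2.486 × 1.312 = 3.26 g, against 3.3 g stated. Power at 3.3 g is 80.8%.

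The section therefore uses an ordinary one-sided comparison of two groups of 90, in absolute units.

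**Step 2. Apply the same kind of test to physical activity.** With p̄ the mean of the two rates:

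- SE₀ = √(2·p̄(1 − p̄)/n)
- SE₁ = √([p₁(1 − p₁) + p₂(1 − p₂)]/n)
- power = Φ[(p₂ − p₁ − 1.645·SE₀)/SE₁]

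*50% versus 59%* (p̄ = 0.545): SE₀ = 0.0742, SE₁ = 0.0739. Power = Φ[(0.09 − 0.1221)/0.0739] = Φ(−0.434) = **33.2%**.

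*50% versus 68%* (p̄ = 0.59): SE₀ = 0.0733, SE₁ = 0.0721. Power = Φ[(0.18 − 0.1206)/0.0721] = Φ(0.824) = **79.5%**.

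Solving for the difference from 50% that gives exactly 80% power yields 18.1 percentage points, which is the stated 18.

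**Step 3. Sample size that the printed 59% would need.** n per group = [1.645·√(2 × 0.545 × 0.455) + 0.842·√(0.25 + 0.2419)]² / 0.09² = (1.158 + 0.590)² / 0.0081 ≈ 378, or 756 in total against 180.

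**Step 4. Sensitivity to the method.**

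| Calculation, 90 per group unless stated | 50% vs 59% | 50% vs 68% |
|---|---|---|
| Pooled normal, one-sided | 33.2% | 79.5% |
| Unpooled normal, one-sided | 33.5% | 80.3% |
| Arcsine, one-sided | 33.3% | 79.5% |
| Fisher exact, one-sided | 28.4% | 76.3% |
| Pooled normal, two-sided | 22.6% | 69.3% |
| Pooled normal, one-sided, 100 per group | 35.6% | 83.1% |

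The last row uses the top of the anticipated enrolment range (180 to 200 in total). No standard two-group calculation brings 50% versus 59% near 80%.

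**Step 5. A possible source of the 59%.** (0.50 + 0.68)/2 = 0.59. The printed value equals the average of the two rates that do give 80% power, so it may be the pooled proportion taken for the target. This is an inference; the article does not say how the figure arose.

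**The case against.** Four points can be made in the article's defence.

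*The two expressions agree as a relative change.* True: 9/50 is exactly 18%, so on that reading they do not contradict each other. But the effect is then 50% versus 59%, and the 80% power is wrong. On the absolute reading the power is right and the 59% is wrong.

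*Another calculation may have been meant.* Some come near 80%: 41% versus 59% (78.3%), or a one-sample test of 59% against 50% in all 180 children (78.3%). A paired before-after test in 90 children reaches 80% for a 9-point change if only about 12% of children change status. None matches the text. The first does not start at 50%, the second is not two groups of 90, and the third is not the between-group comparison and needs a discordance rate that the article does not give. What stands is that 50% versus 68% is the best-fitting reading rather than a documented one, and it assumes that the comparison group stays at 50%. The authors should confirm it against their own calculation.

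*The article is candid about its limits.* The abstract calls this a pilot effectiveness study. The Discussion says that schools were not randomized, that school-level analysis is not possible and that significant between-group changes will be hard to observe. This softens the consequence, but it does not tell the reader that power at 59% is about one third.

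*The corrected figure is itself optimistic.* This stands as a caveat. Assignment is by school, two per arm, about 45 children each (90/2). No intraclass correlation is given. Assuming values of 0.01 to 0.05, the design effect 1 + 44 × ICC is 1.44 to 3.20. Power falls to about 66% to 39% for 50% versus 68%, and to about 26% to 17% for 50% versus 59%. Clustering is a separate issue, but the corrected sentence should say that it assumes independent children.

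**Conclusion.** The concern holds. With 90 children per group and a one-sided 0.05 test, the printed 59% and the stated 80% power cannot both be true. Power for 50% versus 59% is about 33% (28% to 34% across the one-sided methods tried with 90 per group). The difference detectable at 80% power is about 18 percentage points, 50% versus 68%, twice the gain that the parenthesis shows. Reading the 18% as relative does not rescue the statement.

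The result rests on the article's own n, alpha, sidedness and 50% reference rate, on a comparison of two independent groups, and on no allowance for clustering. Because it misstates what the trial can detect on part of a primary aim, it must be corrected.

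**What to change.** Replace the parenthesis with wording such as: 50% in the comparison group versus 68% in the intervention group, an absolute difference of 18 percentage points. Add that power for a 9-point difference (50% versus 59%) is about one third, and that both figures assume independent children. The authors should check the replacement against the calculation that they ran.

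This is a change of wording only. Sample size, design and analysis stay as they are. The cost is that the stated detectable effect becomes less favourable.
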